### **Procedures**

Individual assessments will be conducted at NEUROLAB/UFGM. Assessments will be conducted by a trained researcher blinded to group allocation. All assessed individuals will be informed of the study objectives and will sign the Informed Consent Form. During the initial assessment, eligibility criteria will be verified. For individuals who meet these criteria, sociodemographic data (sex, age, education, socioeconomic level, and occupation) and clinical data (disease duration and Unified PD Rating Scale (UPDRS)) will be collected.(GOULART et al., 2005)For the UPDRS scale, section III will be specifically evaluated, as it is used to assess the impact of the disease on the individual's motor function.(SHEARIN et al., 2021; GOULART et al., 2005).

The included participants will be randomly allocated to the experimental group or control group by the physiotherapist responsible for the intervention. This physiotherapist will be blinded to the assessment performed and previously trained on the intervention procedures. After allocation, individuals in the intervention group will be instructed to maintain their usual healthcare routines and they will receive training on how to use a cane. The training will be conducted at NEUROLAB, UFGM, whose approval has already been obtained, and will be offered in four 40-minute sessions spaced 15 to 22 days apart. In addition, they will be instructed to use the cane during their daily mobility activities, both indoors and outdoors, from the first day of training. To monitor adherence

to cane use, individuals will receive a diary to record their daily use of the device during mobility activities.

Individuals allocated to the control group will be instructed to maintain their usual health care routine and not start using any walking aids during the study period. To control the amount of attention received, individuals in the control group will receive a placebo intervention containing global stretching and health education. The intervention will be carried out at NEUROLAB, UFMG, and will be offered by the same physiotherapist responsible for training the experimental group in four 40-minute sessions spaced 15 to 22 days apart.

All individuals will be reassessed after randomization by the same physiotherapist who performed the first assessment, who will be blinded to the group to which the individual was allocated. Participants will be instructed not to discuss with the assessors the group to which they were allocated. One month after the reassessment, individuals will be reassessed again (follow-up). In these two reassessments, data on the primary and secondary outcome variables will be collected. The individuals in the experimental group will continue to use the cane, but no further instructions regarding its use will be provided during this period between the initial reassessment and the follow-up reassessment. All assessments and training will be conducted during the "on" period of medication. Furthermore, the vital data from all participants will be monitored before and after each intervention session, and the presence of pain and/or fatigue will be questioned during the interventions.

If the experimental group shows improvement in the primary outcome compared to the control group, participants in the control group will be offered the opportunity to undergo cane training after the study is completed.

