## **MATERIALS AND METHODS**

### **Outline**

This is a randomized clinical trial with blinded assessors. The study will be submitted to the Research Ethics Committee of the Federal University of Minas Gerais, and the study protocol will be registered in [the relevant directory/institution].[www.ClinicalTrials.gov](http://www.ClinicalTrials.gov)The study will follow the Consolidated Standards of Reporting Trials (CONSORT) guidelines.(CUSCHIERI, 2019).

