### Satisfaction with using the cane

Satisfaction with cane use will be collected from individuals in the experimental group at the end of their participation in the study. For this purpose, the Quebec User Evaluation of Satisfaction with Assistive Technology (QUEST 2.0) will be used. developed with the goal of evaluating user satisfaction with assistive technology in various aspects such as comfort, safety, weight, ease of use, etc. (Carvalho et al., 2014)The questionnaire has 12 items, scored from zero to five, where higher scores reflect greater patient satisfaction with the assistive technology. (Carvalho et al., 2014)This instrument has already been cross-culturally translated into Brazilian Portuguese and has proven reliable and valid for measuring user satisfaction with assistive walking technology.(Carvalho et al., 2014).

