## APPENDIX II - EVALUATION FORM

### RESEARCH PROJECT:

**EFFECT OF TRAINING AND USE OF A CANE ON THE MOBILITY OF INDIVIDUALS WITH PARKINSON'S DISEASE: A RANDOMIZED CLINICAL TRIAL**

**EVALUATION FORM (initial, re-evaluation or follow-up):** \_\_\_\_\_

**DATE:** \_\_\_\_\_ **TIME:** \_\_\_\_\_ **CODE:** \_\_\_\_\_

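### Assessor blinding is unlikely to hold at reassessment and follow-up, because no step keeps the experimental arm's canes out of the assessor's sight

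*Combined protocol and SAP*

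**What the plan says.** The Outline states the design: "This is a randomized clinical trial with blinded assessors". Under Procedures, reassessment is done by the physiotherapist who did the first assessment, "who will be blinded to the group to which the individual was allocated". The protection given for those visits is "Participants will be instructed not to discuss with the assessors the group to which they were allocated".

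The same section sets the cane regime. For the experimental arm, "they will be instructed to use the cane during their daily mobility activities, both indoors and outdoors, from the first day of training". Between reassessment and follow-up, "The individuals in the experimental group will continue to use the cane". Controls are told not to take up any walking aid. Under Participants, eligibility requires no earlier use of an assistive device.

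The primary outcome is speed from the time over the central 10 m, at usual and at maximum speed, with one familiarization walk and one recorded walk. Step counts and the number and duration of freezing episodes come from the same tests.

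For QUEST 2.0 the protocol says "Satisfaction with cane use will be collected from individuals in the experimental group", at the end of participation. In Appendix II it appears, with the cane diaries, after the heading "EVALUATION FORM (initial, re-evaluation or follow-up".

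**The concern.** Blinding is claimed for the person who measures the primary outcome, but the stated protection covers only what participants say. The intervention is a visible object that one arm is told to carry and the other is told not to have. A participant who follows the instructions would be expected to come to the laboratory with the cane. Training and assessment also share one laboratory, so the assessor may see it between visits.

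The measurements leave room for judgement: when timing starts and stops, how much encouragement is given at maximum speed, how steps are counted, and what counts as a freezing episode. The documents describe no automated timing, scripted encouragement or second timer. With one recorded walk per speed, no repeat measurement averages out an error. If the assessor knows the group, these choices can differ between arms, and analysis cannot remove the resulting bias.

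**Working it through.** The plan gives no figure on blinding to reproduce. The check is a comparison of passages, followed by an illustration on stated assumptions.

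**Does a cane identify the arm?**

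| Step | Source | What it gives |
|---|---|---|
| 1 | Participants | No device use before entry, so no one has a cane of their own at baseline |
| 2 | Procedures | Experimental arm uses the cane indoors and outdoors from the first training day |
| 3 | Procedures | That use continues to follow-up |
| 4 | Procedures | Controls start no aid during the study |
| 5 | Cane diary | Trips far from home are a listed cane situation |
| 6 | Financial budget | 13 canes, equal to the 13 planned per group |

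From 1 to 4, a personal cane seen after baseline indicates the experimental arm if participants comply. Step 5 makes it likely that the cane comes to the visit. Step 6 suggests one cane per experimental participant and no spare for testing.

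**What protects the assessor?** Sealed opaque envelopes, preparation by an uninvolved assistant, and allocation by the intervention physiotherapist all protect assignment. At the reassessment visits only the instruction not to discuss the group applies. No step concerns arrival, storage of canes, a neutral cane, or a check of whether blinding held.

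**Does the walking test itself reveal the arm?** Appendix II has with-cane and without-cane versions of the gait speed test and the TUG, each with a test-order field and no group restriction. The outcome section does not say which version is primary, or whether controls do the with-cane version after baseline. If both arms do both, a cane in the test reveals nothing. If only the experimental arm is tested with a cane, concealment during that test is impossible.

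**Illustration of scale (the timing shifts, SDs and walking speeds are assumptions).** Time is 10/v. If it is recorded e seconds short, speed rises by 10/(10/v − e) − v.

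- At v = 0.8 m/s the time is 12.5 s. For e = 0.1, 0.3, 0.5 s: 10/12.4, 10/12.2, 10/12.0, giving +0.006, +0.020, +0.033 m/s.
- At v = 1.1 m/s (the entry ceiling) the time is 9.09 s. For the same e: +0.012, +0.038, +0.064 m/s.
- Times recorded long give shifts of similar size downward. For example, at 0.8 m/s with 0.5 s added, 10/13.0 − 0.8 = −0.031 m/s.

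Suppose there is no true effect and a bias b is present in one arm only. A two-sided 5% two-group t test then has noncentrality (b/SD)·√(n/2) on 2n − 2 degrees of freedom. With n = 9 (the calculated size) or 13 (all randomized), the rejection rates are:

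| SD (m/s) | n per group | b = 0.02 | b = 0.04 | b = 0.06 |
|---|---|---|---|---|
| 0.10 | 9 | 6.8% | 12.6% | 22.4% |
| 0.10 | 13 | 7.8% | 16.5% | 31.2% |
| 0.25 | 9 | 5.3% | 6.2% | 7.7% |
| 0.25 | 13 | 5.4% | 6.8% | 9.0% |

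For example, with SD 0.10, n = 9 and b = 0.06, the noncentrality is 0.6 × √4.5 = 1.27 on 16 degrees of freedom. The planned test is a repeated measures ANOVA, so these rates show scale only.

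**The case against.** The strongest defence is that the plan has real safeguards and never says the assessor sees a cane. Allocation is concealed and carried out by someone other than the assessor, and the analyst is blinded. Entrants can walk without a device, and arrival at the visit is not described. This stands in part. It would be wrong to say that the non-disclosure request is the plan's only safeguard; it is the only one acting at the reassessment visits. Analyst blinding does not help, because a bias would already be in the recorded times.

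A reader might infer three stronger things that the documents do not support:

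- **That participants will certainly arrive with the cane and blinding will fail.** Arrival is an inference, although it is what following the instructions would produce.
- **That the assessor's own form gives the group away.** The diaries are filled in by participants, and no passage says the assessor reads them. QUEST 2.0 comes at the end of participation with no administrator named, so it cannot unblind the first reassessment. It need not affect follow-up either, if it is given last or by someone else. Its place after the evaluation form heading does not show who handles it, and the with-cane tests are not restricted to one arm.
- **That the bias would favour the cane.** The Introduction reports studies in which canes slowed gait, so an assessor's expectation could go either way.

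**Conclusion.** The point holds: blinding of the assessor at reassessment and follow-up is unlikely to survive the plan as written, and no step protects it from sight of the cane. This rests on participants following the cane instructions and bringing the cane to visits, neither of which the plan prevents.

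The effect on the result cannot be estimated from the documents, which give neither the SD of gait speed nor the timing method. In the illustration, the false-positive rate ranges from barely above 5% to about 31%. The upper end needs both the smallest assumed SD and the largest assumed bias. Those figures show why a cheap protection is worth having; they do not predict the bias. A bias against the cane is as possible as one in its favour.

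**What to change.** Amend the reassessment text in Procedures and split Appendix II:

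1. Non-assessor study staff, for example the intervention physiotherapist, receive participants at each reassessment and store personal canes before the assessor meets them.
2. Both arms do the same with-cane and without-cane tests in the same way. Any with-cane test uses a laboratory cane adjusted to the participant. State which condition is primary.
3. QUEST 2.0 and the diaries go on a separate form that the assessor does not see. QUEST 2.0 is completed after the last test, by the participant alone or with someone other than the assessor and the treating physiotherapist. Item 11 rates professional services, so the treating physiotherapist should not collect it.
4. The assessor records a guess of the group at each reassessment, and the guesses are reported.
5. If a test condition makes concealment impossible, describe the blinding as limited for that outcome.

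The cost is minor visit logistics with existing staff, a divided form, and possibly one extra cane (R$50 at the budgeted unit price). A laboratory cane is not the one the participant trained with and may not hide trained skill. The recorded guess would help show whether concealment worked.

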### **Intervention of the experimental group**

The height of the cane will be adjusted so that each individual's elbow is at approximately 30 degrees of flexion. (BRYANT et al., 2012) Regarding which side to use the cane on, patients will be instructed to use the device on the side they use most (dominant) or the side with the least impairment. (GLISOI et al., 2012).

The gait training protocol will be based on the Exercise Guidelines for Gait Dysfunction in PD. (NI et al., 2018) According to these guidelines, for gait-related outcomes, specific gait training should be preferred over general exercise programs. (NI et al., 2018) Furthermore, supervised training is recommended, as it is associated with

greater improvement in motor function.(NI et al., 2018)The authors further suggest that the program be initiated at a comfortable, auto-selected driving speed, progressing to maximum speeds.(NI et al., 2018)Therefore, the training will be conducted under the supervision of a physiotherapist, and the training protocol will include gait training on different surfaces and speeds, using a cane, divided into the following stages: 1) gait training on the ground at a comfortable speed, on a flat and stable surface (warm-up); 2) gait training on the ground at a comfortable speed, on a steep and stable surface (ramp); 3) gait training on the ground at maximum speed, on a flat and stable surface; 4) gait training on the ground at a comfortable speed, on a flat and stable surface (cool-down). Stages 1 and 4 will last 5 minutes each. Stages 3 and 4 will last 10 minutes each. A break will be given for the patient to rest between stages and whenever necessary. In addition, at the beginning of each training session, individuals will have the opportunity to ask any questions they may have about using the cane in their daily life context.

### **Control group intervention**

The control group will receive a placebo intervention based on protocols from previous studies. (Avelino et al., 2018; Martins et al., 2017) The intervention will include global stretching exercises for upper and lower limbs and health education. During the intervention, 20 minutes of static global stretching will be performed, followed by 20 minutes of general health care guidance. The stretches will be performed in three sets of 30 seconds each and will involve different muscle groups. (Avelino et al., 2018; Martins et al., 2017) If the participant is unable to perform self-stretching, the researchers responsible for implementing the intervention will provide assistance. Guidance on general health care will include information on PD and fall prevention and will be based on the Portuguese version of the European Physiotherapy Guideline for PD (CAPATO et al., 2015).

### **Outcome measures**

#### **Primary outcome measure**

##### Gait speed

Gait speed will be measured using the 10-meter Gait Speed Test. This will be done using a 14-meter corridor where the central 10 meters will be used to calculate gait speed. The first two meters and the last two meters will be disregarded from the assessment as

they correspond to the individual's acceleration and deceleration time during walking. The individual will be instructed to walk the indicated space first at their usual speed and then at their maximum speed. Gait speed will be calculated based on the time taken for the individual to cover the central 10 meters. This test has adequate measurement properties for evaluating this outcome in individuals with PD and is widely used in clinical practice.(LIM et al., 2005).An initial test will be conducted to familiarize the patient, followed by a second test to record the measurement. (Lindholm et al., 2018)If the individual experiences any freezing episodes during the test, the number of episodes and the freezing time will be recorded. Bloem, 2016).

### **Secondary outcome measures**

#### Stride length and cadence:

For measuring step length and cadence, the number of steps taken during the 10m speed test will be counted.(CAPATO et al., 2015).To calculate average stride length, the total distance is divided by the number of steps. To calculate cadence, the number of steps is divided by the time taken to cover 10 meters, in seconds.(CAPATO et al., 2015).

#### Gait confidence

Confidence in gait will be assessed using the Gait Efficacy Scale-Brazil (mGES-Brazil).(AVELINO et al., 2018)The mGES-Brazil is a ten-item scale that assesses an individual's confidence during gait in challenging circumstances, such as walking on different surfaces.(AVELINO et al., 2018)Each item on the scale is individually scored on a Likert scale from zero to ten points, with higher scores indicating greater confidence.(AVELINO et al., 2018)The scale has already been cross-culturally adapted for Brazilian Portuguese and has shown adequate measurement properties for assessing this outcome.(AVELINO et al., 2018).

#### Functional mobility

Functional mobility will be assessed using the Timed Up and Go (TUG) test. The TUG is an easy-to-administer test that measures the time it takes an individual to stand up from a chair, walk 3 meters, turn around, and return to the chair.(CAPATO et al., 2015)This test also presents adequate measurement properties for evaluating this outcome in individuals with PD, and a TUG time > 8.5 seconds for completing the test is associated

with a higher risk of falls in individuals with PD.(CAPATO et al., 2015).To measure this outcome, an initial test will be conducted to familiarize the patient.(CAPATO et al., 2015). Immediately after the test, it will be performed again and the time of the second test will be recorded.(CAPATO et al., 2015)As with the gait speed test, the number and duration of possible episodes freezing will be recorded (Bloem, 2016).

### Freezing of gait

Freezing during gait will be assessed using the Gait Freezing Questionnaire (*Freezing of gait questionnaire*, FOG-Q). This questionnaire has six items whose objective is to evaluate freezing during gait in patients with PD (Baggio et al., 2012; Oliveira, 2010).The instrument has already been cross-culturally translated into Brazilian Portuguese (Baggio et al., 2012)Furthermore, the questionnaire has adequate measurement properties and is considered reliable for screening and measuring the severity of frostbite, as well as for evaluating this outcome after interventions. (Baggio et al., 2012)In addition to the questionnaire, the number and duration of freezing episodes that patients experience during the gait speed test and the TUG will be reported.

### Satisfaction with using the cane

Satisfaction with cane use will be collected from individuals in the experimental group at the end of their participation in the study. For this purpose, the Quebec User Evaluation of Satisfaction with Assistive Technology (QUEST 2.0) will be used. developed with the goal of evaluating user satisfaction with assistive technology in various aspects such as comfort, safety, weight, ease of use, etc. (Carvalho et al., 2014)The questionnaire has 12 items, scored from zero to five, where higher scores reflect greater patient satisfaction with the assistive technology. (Carvalho et al., 2014)This instrument has already been cross-culturally translated into Brazilian Portuguese and has proven reliable and valid for measuring user satisfaction with assistive walking technology.(Carvalho et al., 2014).

### **Sample calculation**

Twenty-six individuals will be included in this study. The sample size calculation was performed considering the clinically important difference in the primary outcome measure, gait speed. (Hass et al., 2014)Considering a significance level ( $\alpha$ ) of 5% and a

power of 0.80, an  $n=9$  was found for each group. Therefore, a sample size of 18 individuals. Assuming a sample loss of 30% of individuals throughout the study, a total sample of 26 individuals was determined, with 13 in each group.

### **Data analysis**

The analysis will be performed by an independent researcher, blinded to the randomization of the groups, using intention-to-treat and per-protocol analysis. The normality of the data will be tested for all continuous numerical variables. Descriptive statistics will be used to characterize the sample and to investigate satisfaction with the use of the cane. The difference between the groups for the other outcome variables (gait speed, gait confidence, cadence, step length, functional mobility, freezing of gait) will be evaluated using repeated measures ANOVA, considering the measurements collected at the initial assessment, after training, and at follow-up. All statistical analyses will be performed using SPSS statistical software (SPSS Inc., Chicago, IL, United States). A significance level of  $\alpha=5\%$  will be established for all inferential analyses.

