### **Randomization**

Individuals will be randomly assigned to the experimental and control groups. The allocation ratio will be 1:1, according to a randomization plan generated by a website. The randomization sequence will be kept in sealed opaque envelopes. The envelopes will be prepared before the start of the study by a research assistant not involved in the study.

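### Intention-to-treat is promised, but a three-visit repeated-measures ANOVA with no missing-data method would, as classically run, analyse only completers: about 18 of 26 at the plan's own loss rate

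*Combined protocol and SAP*

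**What the plan says.** Data analysis states that the work will be done "using intention-to-treat and per-protocol analysis". Neither analysis set is defined. For gait speed (primary) and the five other compared outcomes, the group difference "will be evaluated using repeated measures ANOVA, considering the measurements collected at the initial assessment, after training, and at follow-up". The software is SPSS; the procedure is not named.

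Sample calculation arrives at 9 per group ("Therefore, a sample size of 18 individuals") and continues: "Assuming a sample loss of 30% of individuals throughout the study", "a total sample of 26 individuals was determined, with 13 in each group".

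No section gives an imputation rule, a mixed model, an assumption about missing data or a missing-data sensitivity analysis.

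**The concern.** Three statements in the plan do not fit together: everyone randomised is to be analysed, almost a third are expected to be lost, and the named method in its usual form needs a complete set of three measurements per person. Under that method a participant who attends the post-training visit and misses follow-up one month later loses the post-training value as well, although it was collected.

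At stake is the randomised comparison for every outcome that the arms are compared on. If leaving is related to response, and differently so in the two arms, the completers are no longer comparable groups. The result labelled intention-to-treat might also hardly differ from the per-protocol result, so that reporting both would give little reassurance.

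**Working it through.** **1. The plan's own sample size.** Inputs from Sample calculation: 18 evaluable (9 per group), 30% loss.

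- Total: 18 / (1 − 0.30) = 25.7, rounded up to 26.
- Per group: 9 / 0.70 = 12.9, rounded up to 13.

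Both match the plan.

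**2. Complete cases at that loss.** 26 × 0.70 = 18.2 (9.1 per arm). Left out: 26 − 18.2 = 7.8, about 8 of 26, or 31%. At other loss rates: 10% gives 23.4, 20% gives 20.8, 40% gives 15.6. If each participant independently has a 30% chance of loss, the central 95% range of completers is 13 to 23.

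**3. What is thrown away.** Assume the 30% is spread evenly over the two post-baseline visits.

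- Loss per visit: 1 − √0.70 = 0.163.
- Attend post-training: 26 × 0.837 = 21.8.
- Of these, lost before follow-up: 21.8 − 18.2 = 3.6. Their post-training values exist and would be discarded.
- Baseline only: 26 − 21.8 = 4.2. No model of post-baseline values recovers these.

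**4. Power.** The plan gives neither a difference nor an SD. Solving backwards, 9 per group at 80% power (two-sided 5% t-test) implies a standardised difference of 1.41; 13 per group would then give about 93%. Analysing 18 is what the trial was sized for.

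**5. Possible bias (illustration; none of these inputs is in the documents).** Assumed: 13 per arm, correlation 0.7 between any two visits, no true effect, 30% loss. Where loss is selective, its probability is logistic in the standardised change to post-training, with slope 1, 2 or 3. There were 6,000 replicates per setting. The quantity is the completers-only difference in change at post-training.

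| Pattern of loss | Bias (SD) | False positives |
|---|---|---|
| Unrelated to outcome | about 0 | about 5% |
| Equally selective in both arms | about 0 | about 5% |
| Spread over both visits; early loss random, late loss selective in one arm | 0.11 to 0.19 | about 5 to 8% |
| All after post-training, selective in one arm | 0.19 to 0.34 | 8 to 15% |

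A closed-form check gives the ceiling. The SD of change is √(2 × (1 − 0.7)) = 0.775. If exactly the worst 30% of changers leave one arm, the mean standardised change of those who stay is 0.348 / 0.70 = 0.497 (0.348 being the normal density at the 30% point). The bias is then 0.497 × 0.775 = 0.38 SD at post-training, and half of that, 0.19 SD, at follow-up.

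The false-positive rates are for the post-training difference. In the last row of the table, the planned group-by-time test rejects in about 7 to 12% of replicates.

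**6. What using all post-training values achieves.** In the last two rows of the table, keeping every observed post-training value brings the bias to about 0. If half of the losses come before the post-training visit and are selective too, that comparison is itself biased by 0.08 to 0.14 SD, with 6 to 7% false positives.

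**The case against.** **Listwise deletion is inferred.** The plan names an ANOVA and a software package, not a procedure. SPSS can also impute and fit mixed models, and authors who list intention-to-treat and per-protocol separately may have some way of retaining participants in mind. This stands to the extent that one cannot say that an intention-to-treat analysis is impossible under this plan. It does not remove the gap: the method is unstated, the default reading gives completers, and leaving the choice open allows it to be made after the data are seen.

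**A reader might infer that the bias favours the cane.** The Introduction reports earlier studies in which single-point canes slowed walking, and only the experimental arm must use a cane and keep a diary, so selective loss there is plausible. But the documents do not say who will leave. Control participants receive stretching and education, are told not to start a walking aid, and are offered cane training only after the study and only if it worked; they too could leave selectively. The direction is open.

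**A reader might take 15% as the error rate of the planned test.** It is the worst setting shown, for a different contrast, and it needs all loss to follow the post-training visit. Sample calculation places loss throughout the study. With random or equally selective loss, the excess disappears.

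**A reader might infer a power shortfall.** There is none against plan, as step 4 shows. Enlarging the sample protects precision, though; it does not protect against selective loss.

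**Conclusion.** The concern holds as a conflict between the stated analysis set and the stated method. Run in its classical form, the ANOVA turns the analysis labelled intention-to-treat into a completers analysis of about 18 of 26 participants, and drops post-training values already collected (about 3.6 participants' worth if loss is even over the two visits). The count rests on the plan's 30% loss and on the default SPSS procedure.

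The size of any bias is not known. Under the assumptions shown it lies between about 0 and 0.34 SD at post-training, and it could go either way. The missing rule is certain; the bias figures only show that it can matter. It should be settled before analysis because it touches the primary outcome and every other between-group comparison.

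**What to change.** In Data analysis:

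- Define the intention-to-treat set as all randomised participants in the arm assigned.
- Make the primary intention-to-treat analysis a linear mixed model (SPSS MIXED, REML, Satterthwaite degrees of freedom) with group, visit and group-by-visit, and baseline as a covariate, using every available post-baseline value. State the covariance structure for the two post-baseline visits in advance.
- Report by arm the number of participants with baseline only, since they contribute no outcome to this model. Because the model assumes missing at random, add a multiple-imputation or missing-not-at-random sensitivity analysis.
- Define the per-protocol set and label that analysis a sensitivity analysis.

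If the authors already intend a mixed model or imputation, saying so in the same place closes the gap.

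The cost is about one paragraph, in the same software and with no new data. The downsides are somewhat more analysis work and reliance on missing at random in the primary model. The sensitivity analysis is there to test that assumption.
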